## Abstract

**Background:**

Several years ago, repetitive transcranial magnetic stimulation (rTMS) of the auditory cortex has been introduced as a treatment approach for chronic tinnitus. Even if this treatment is beneficial for a subgroup of patients, the overall effects are limited. This limitation may be due to the fact that the auditory cortex is only one of several brain areas involved in tinnitus. Whereas auditory areas are considered to code for tinnitus loudness, conscious perception of and attention allocation to tinnitus is supposed to be reflected by network activity involving frontal and parietal cortical areas. The aim of the present study is to influence this frontoparietal network more efficiently by perturbing the most important nodes with rTMS.

**Methods/design:**

This is a randomized, double-blind, parallel-group study. Patients receive rTMS treatment on 10 consecutive working days using either the multisite rTMS protocol (left dorsolateral prefrontal, 1,000 stimuli, 20 Hz; left temporoparietal, 1,000 stimuli, 1 Hz; right temporoparietal stimulation, 1,000 stimuli, 1 Hz) or a single-site protocol (unilateral stimulation of the temporoparietal cortex, 3,000 stimuli, 1 Hz). Individuals aged 18 to 70 years with chronic tinnitus ≥6-month duration and a Tinnitus Handicap Inventory score ≥38 are recruited for the study. A total of 50 patients are needed to detect a clinical relevant change of tinnitus severity (α = 0.05; 1 – β = 0.80). Primary outcome measures are the change in the Tinnitus Questionnaire score from baseline to the end of treatment as well as the number of treatment responders as defined by a reduction in the Tinnitus Questionnaire score of ≥5 points. Furthermore, changes in brain structure and activity are assessed using (functional) magnetic resonance imaging and electroencephalography in the resting state. Those measurements are also performed in 25 healthy control subjects.

**Discussion:**

This study is designed to reveal whether network stimulation is superior to single-site stimulation in the treatment of chronic tinnitus. Furthermore, the comparison between tinnitus patients and healthy controls and the longitudinal effects of both rTMS treatment protocols on brain structure and function allow inferences to be made about the neural correlates of tinnitus.

**Trial registration:**

Clinical Trials:
NCT01663324

## Background

Subjective tinnitus is the auditory sensation of sound or noise in the absence of an acoustic stimulus. About 10 to 15% of adults in western societies report to suffer from tinnitus
[1]. Tinnitus may have many etiologies and can involve severe psychological distress
[2]. The neurobiological mechanisms underlying tinnitus are still incompletely understood, and causally oriented treatment options are scarce. Neuroimaging and electroencephalography (EEG)/magnetoencephalography (MEG) studies have revealed increased neural activity in central auditory pathways
[3-8] and have demonstrated alterations in the frequency spectrum power during resting state activity in tinnitus patients
[9]. Based on the hypothesis that repetitive transcranial magnetic stimulation (rTMS) can reduce tinnitus by interfering noninvasively with abnormal activity in the auditory cortex, this method has been investigated for the treatment of tinnitus
[10-12]. rTMS treatment in tinnitus patients is so far still of questionable clinical benefit
[13], and therefore is not yet ready for application in the clinical routine. Taking into account the lack of other causally oriented treatment options for tinnitus, rTMS treatment is nevertheless considered a promising technique, and miscellaneous optimization strategies have been proposed
[14].

In the current study an innovative optimization approach is used that is motivated by the recent finding in tinnitus patients that alterations of brain activity are not restricted to the auditory cortex but involve a network of both auditory and nonauditory brain regions
[15-17]. Important nodes of this tinnitus network include the left and right auditory cortex, the anterior and posterior cingulate cortex, left frontal and parietal cortical areas. These areas and their functional interconnection are thought to reflect the conscious perception of tinnitus and the attention allocation to the percept
[17-20]. Aiming to increase the therapeutic efficacy of rTMS, we propose a new multisite stimulation protocol interfering with this tinnitus network at several nodes. The multisite stimulation protocol consists of high-frequency left dorsolateral prefrontal stimulation followed by left and right temporoparietal low-frequency rTMS and has already been tested in a pilot study
[21]. This pilot study showed promising effects. The new protocol should now be examined in a double-blind randomized controlled trial (blinding of the patient and the clinicians involved in ratings and data analysis) to determine whether it is able to disrupt the altered activity within the tinnitus network. As tinnitus has been shown to be associated with altered connectivity patterns
[15-17], EEG and functional magnetic resonance imaging (MRI) measurements will be used to replicate those results and to examine the effect of rTMS on these alterations.

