### Control subjects

To potentially replicate and expand findings concerning the neural correlates of tinnitus, 25 control subjects without tinnitus but matched for age, gender and hearing function are examined once using EEG, MRI, functional MRI and all questionnaires (except for the tinnitus-specific ones). Inclusion criteria for the control subjects are age between 18 and 70 years and written informed consent. Exclusion criteria are identical to the exclusion criteria for patients except for the first three criteria.

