### Treatments

On the first treatment day, patients are randomized to one of the following two parallel groups.

The multisite group is treated with the new multisite rTMS protocol consisting of high-frequency stimulation of the left dorsolateral prefrontal cortex (20 Hz, 1000 stimuli/day, which are applied in 20 trains with an intertrain interval of 25 seconds) followed by 1000 stimuli at 1 Hz over the left temporoparietal cortex and 1000 stimuli at 1 Hz over the right temporoparietal cortex. The stimulation parameters have been chosen according to a pilot study
[21] with a slight modification with respect to the number of stimuli. A detailed explanation for the choice of protocol can be found in Lehner and colleagues
[21].

The single-site group is treated with a single-site rTMS protocol consisting of 3000 stimuli/day that are applied at 1 Hz over the temporoparietal cortex contralateral to the tinnitus percept
[26]. Based on former studies, the left hemisphere is treated in case of bilateral tinnitus (for example
[27]). Since the goal of this study is to demonstrate superiority of the multisite stimulation over the current standard approach (stimulation of the temporoparietal cortex), an active stimulation protocol was chosen for comparison instead of placebo stimulation.

All patients receive 10 treatment sessions on 10 consecutive working days. The total number of stimuli per session is identical for both treatment groups (3000 stimuli per session). rTMS is performed with an intensity of 110% of the resting motor threshold but never higher than 60% of the maximal stimulator output. The resting motor threshold is determined at the beginning of the first treatment session and is defined as the minimal intensity at which at least five of 10 motor evoked potentials are 50 μV in amplitude in the right abductor digiti minimi. rTMS treatment is performed with a Medtronic MagPro Option stimulator (Medtronic, Minneapolis, MN, USA) connected to a 70 mm figure-of-eight coil. The coil is held tangential to the scalp with the handle pointing upwards. The temporoparietal cortices are localized using the 10–20 System by placing the coil between the temporal (T3/T4) and the parietal (P3/P4) EEG electrode sites
[28,29]. The dorsolateral prefrontal cortex is targeted by centering the coil 6 cm anterior from the part of the motor cortex that had been used for defining the resting motor threshold.

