#### Statistical analysis

Missing data entries are handled with the last observation carried forward method. For the comparison of treatment responders in both groups, a chi-square statistic is calculated. For all secondary outcomes, an analysis of variance is used with the between-subjects factor group (multisite rTMS vs. single-site rTMS) and the repeated-measures factor time (baseline vs. end of treatment vs. all follow-up time points). EEG and (functional) MRI data are analyzed with MatLab-based analytic software (MathWorks, Natick, MA, USA; EEGLAB; FieldTrip; SPM). For both EEG and functional MRI data, different exploratory analyses focusing predominantly on connectivity measures will be done. As it is hypothesized to find altered connectivity patterns in tinnitus patients, imaging/EEG data of both patient groups are compared with data for the control group (baseline measurements of the tinnitus groups vs. single measurement of the controls). Furthermore, longitudinal analyses will be performed to test for a change of the connectivity patterns from before to after rTMS treatment (contrast: pre rTMS vs. post rTMS). Correlations of imaging data and questionnaire scores are used to identify potential predictors for rTMS outcome. As the present protocol has a clinical focus, we do not go into detail concerning the EEG and functional MRI analyses at this point.

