## Discussion

rTMS has been used as a treatment approach for chronic tinnitus for several years. Results from clinical trials are heterogeneous; in summary, the effect size of rTMS treatment over the auditory cortex has been shown to be rather small. The idea of interfering with altered brain activity via noninvasive brain stimulation is plausible, however, and the efficacy of a specific treatment protocol depends on the quality of the neurobiological model underlying that protocol. During the last few years, knowledge about the neurobiological mechanisms of tinnitus has advanced
[20]. Neuroscientists have moved away from a model restricted to the auditory system towards the concept of a more widespread tinnitus network. This new model of tinnitus can and should now be used to improve rTMS treatment. The attempt to adapt rTMS treatment to the network model brings several methodological difficulties about which had to be dealt with in the design of this trial. The tinnitus network as described by Schlee and colleagues involves several brain regions, all of which can be stimulated with different frequencies in a different order and with a varying number of stimuli
[17]. One of the many possible treatment protocols therefore had to be chosen
[21]. The attempt of this study is not to find the best of all possible protocols but to determine whether a multisite stimulation protocol based on recent studies on the tinnitus network is superior to the standard protocol used in tinnitus treatment. This reason is also why the standard protocol was used as control treatment instead of a placebo control. Having these constraints in mind, the study is capable of providing useful information about a new way to use rTMS in tinnitus patients. By using EEG and (functional) MRI we are able to determine whether both treatment protocols induce different changes in brain structure and function and whether multisite stimulation serves the purpose of interfering with the tinnitus network. Furthermore, the comparison between clinical changes and changes in neuroimaging findings over time provides a unique opportunity for further specifying the exact role of the neuronal network changes underlying tinnitus perception and distress.

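### The trial cannot show that multisite rTMS disrupts the tinnitus network in absolute terms, because nobody is re-measured without active stimulation; it can show only a difference from single-site rTMS

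*Protocol article*

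**What the plan says.** The Background gives two mechanistic purposes. The new protocol is to be tested "to determine whether it is able to disrupt the altered activity within the tinnitus network", and EEG and functional MRI are to be used to replicate published connectivity findings and "to examine the effect of rTMS on these alterations". The Discussion says the imaging will allow the investigators to determine two things: whether the two protocols induce different brain changes, and "whether multisite stimulation serves the purpose of interfering with the tinnitus network". The second is a statement about multisite stimulation itself, separate from the comparison.

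The design that has to support this is as follows.

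- Treatments: "an active stimulation protocol was chosen for comparison instead of placebo stimulation". Also "All patients receive 10 treatment sessions on 10 consecutive working days", so both arms are stimulated.
- Control subjects: "25 control subjects without tinnitus but matched for age, gender and hearing function are examined once".
- Procedures: patients have MRI, functional MRI and EEG at a baseline visit and again after rTMS, with one further EEG at 3 months. Every repeat measurement follows active stimulation.
- Statistical analysis: controls enter through a comparison with the patients' baseline. The longitudinal imaging analyses are "to test for a change of the connectivity patterns from before to after rTMS treatment".
- Objectives: a comparison of brain changes between multisite and single-site rTMS is listed as an aim, as is the correlation of successful treatment with brain change.

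**The concern.** A before-after contrast in treated patients answers a causal question only if something shows what would have happened over the same interval without treatment. Here nothing does. Repeating a resting-state scan or EEG can change the result through familiarity, arousal or equipment drift. Patients can also change spontaneously, and any single measurement is subject to regression to the mean. All of these would appear in the before-after contrast together with any rTMS effect.

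What is at stake is the mechanistic conclusion. A shift in connectivity after multisite treatment could be reported as evidence that the network was disrupted when rTMS played no part. The correlation of brain change with clinical improvement has the same weakness: spontaneous fluctuation that moves both the symptom score and the brain measure would produce a correlation without any rTMS effect.

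**Working it through.** **What each comparison estimates.** Let M and S be the true effects of multisite and single-site rTMS on an imaging measure, and D the mean change that would occur over the same interval without stimulation.

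- Mean before-after change, multisite arm: M + D.
- Mean before-after change, single-site arm: S + D.
- Mean before-after change, arms pooled in equal numbers: (M + S)/2 + D.
- Healthy controls: one measurement, so no change score and no information on D.
- Randomised difference in change: (M + D) − (S + D) = M − S.

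The claim in the Background and Discussion is about M. No planned comparison isolates M, because D cannot be estimated from any group. The between-arm aim in the Objectives estimates M − S without bias from D. If M and S are equal and both non-zero, that difference is zero although the network has been altered.

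**The plan's own figures.** There is none for imaging. The sample size section (42 patients, raised to 50) is for the clinical group-by-time interaction on the Tinnitus Questionnaire and does not bear on this point. It supplies only the numbers used below: 25 per arm, 50 in total.

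**Illustration of size.** Assume M = S = 0, and let d be D divided by the standard deviation of the change score. The document gives no value for d, so a range is shown. For a two-sided 5% paired t-test with n patients:

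- degrees of freedom n − 1, noncentrality d × √n;
- chance of a significant result = P(T > c) + P(T < −c), where T is noncentral t and c is the 97.5% point of the central t distribution.

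For d = 0.2 the noncentrality is 0.2 × √25 = 1.00 with one arm and 0.2 × √50 = 1.41 with both arms pooled, giving 16.1% and 28.4%.

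| Assumed drift d | One arm, n = 25 | Both arms pooled, n = 50 |
|---|---|---|
| 0 | 5.0% | 5.0% |
| 0.1 | 7.7% | 10.7% |
| 0.2 | 16.1% | 28.4% |
| 0.3 | 30.2% | 54.8% |
| 0.4 | 48.4% | 79.2% |
| 0.5 | 67.0% | 93.4% |

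Under the same assumptions the between-arm test of change stays at 5%, because equal drift cancels. The table shows the mechanism for a single imaging measure; it does not predict this trial's error rate.

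**The case against.** The strongest reply has three parts.

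**The active comparator is deliberate and justified.** The Treatments section and the Discussion both explain that the goal is superiority over the standard protocol. This stands. Nothing here says a placebo arm was needed for that goal. But a comparator chosen for a relative question does not also answer an absolute one.

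**The imaging analyses are exploratory, and the article says it does not detail them.** This also stands, and it limits the weight of the point. It does not remove it: the gap is in who is measured and when, which no analysis plan can supply, and the Discussion states without qualification that the question can be determined.

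**The between-arm comparison of brain changes is already an aim.** True, and the fix relies on it. However, the Discussion names the absolute claim alongside the comparison.

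Two stronger readings are tempting, and the document does not support them.

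- A reader might infer that connectivity features will be picked because they look abnormal in this trial's own baseline patient-control comparison and then followed from that same baseline, which would build in movement towards the control value. No such selection step is stated. In the Background, the alterations referred to are the published ones, and the Statistical analysis section lists the patient-control comparison and the longitudinal analysis separately. Any percentage for such a bias would also need an assumed true patient-control difference, a selection threshold and a reliability, none of which is given.
- A reader might infer that the entry threshold of 38 on the Tinnitus Handicap Inventory makes the imaging measures regress. That requires transient fluctuation in the questionnaire score to be correlated with transient fluctuation in the EEG or fMRI measure, and the document gives no basis for this.

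**Conclusion.** The point holds for the absolute mechanistic claim. As designed, the trial can show whether multisite rTMS changes the network differently from single-site rTMS. It cannot attribute a before-after change in either arm, or its correlation with clinical improvement, to rTMS. This follows from the stated design: both arms active, controls measured once, and repeat imaging only after stimulation.

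The size of any misattribution is unknown, because it depends on drift that the document does not quantify. The percentages above rest on assumed drift of 0.1 to 0.5 standard deviations of the change score, equal in both arms, and on no rTMS effect.

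The scope is limited to exploratory imaging aims. The Tinnitus Questionnaire endpoints, the responder comparison and the randomised between-arm comparison of brain changes are not affected. It would be wrong to infer that the trial's main comparison is invalid. The change is still worth making, because it alters what the trial may conclude about mechanism.

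**What to change.** 1. Statistical analysis: state that any conclusion about rTMS effects on the network rests on the group-by-time term, that is, the multisite versus single-site difference in change of the EEG or fMRI measure. Label the before-after contrast, and its correlation with clinical improvement, as descriptive.
2. Background and Discussion: limit the claim to multisite relative to single-site rTMS, and say that change within an arm cannot be attributed to rTMS because no unstimulated group is re-measured.

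This costs wording only, with no additional scans or patients. The price is a narrower claim: if the arms do not differ, whether multisite rTMS disrupts the network at all stays unanswered.

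Keeping the absolute claim would require a sham or unstimulated tinnitus group re-measured over the same interval, which is a different and larger study. A second measurement of the healthy controls would capture retest and scanner drift, but not spontaneous change or regression to the mean in patients, so it would not be enough alone.

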### Objectives

Based on the findings in the pilot study, we hypothesize that the reduction of the Tinnitus Questionnaire (TQ) score as well as the number of treatment responders after 10 days of rTMS treatment and after follow-up periods of 3 and 6 months are higher when patients are treated using the new multisite stimulation protocol in comparison with single-site stimulation of the temporoparietal cortex. Treatment response is defined as an improvement of ≥5 points in the TQ score
[22]. Further aims of the study are as follows: to compare multisite stimulation with single-site stimulation with respect to a change of tinnitus severity as measured by the TQ, the Tinnitus Handicap Inventory (THI) and numeric rating scales assessing the loudness and annoyance of the tinnitus percept (baseline vs. end of treatment and all follow-up visits); to compare single-site stimulation with multisite stimulation with respect to a change in secondary outcomes such as quality of life, hyperacusis and depressive symptoms (baseline vs. end of treatment and all follow-up visits); to replicate and expand findings concerning the neural correlates of tinnitus using resting state EEG, MRI and resting-state functional MRI; to examine whether successful treatment with rTMS is correlated with changes in brain structure and activity; to examine whether treatment with multisite rTMS induces different brain changes than treatment with single-site rTMS (we assume that network alterations associated with tinnitus can be influenced more effectively using multisite stimulation as compared with single-site rTMS); and to determine whether brain structure and activity as measured by EEG and functional MRI at baseline are predictive for treatment response.

## Methods/design

### Design of the trial

This trial is a two-arm, randomized, double-blind parallel-group study of 2 weeks of rTMS treatment plus 12-week and 24-week follow-up visits in patients with moderate to severe chronic subjective tinnitus. The trial is performed at the multidisciplinary tinnitus clinic at the University of Regensburg. Fifty patients are randomly assigned to a 2-week rTMS treatment either with a single-site rTMS protocol or with the new multisite protocol.

### Study population

#### Patients

Fifty patients are included in the study. Patients are eligible for study participation if they meet the following inclusion criteria: diagnosis of chronic subjective tinnitus; duration of tinnitus ≥6 months; score ≥38 on the THI at screening; age between 18 and 70 years; and written informed consent.

The study exclusion criteria were: objective tinnitus; treatable cause of the tinnitus; prior treatment with transcranial magnetic stimulation; clinically relevant unstable psychiatric, internal or neurological comorbidity; history or evidence of significant brain malformation, neoplasm, head injury or cerebral vascular events; metal objects in and around the body that cannot be removed, cardiac pacemakers, other electronic implants; history of seizures or epileptic activity; pregnancy; alcohol or drug abuse; and intake of benzodiazepines ≥1 mg lorazepam/day (or equivalent doses of other benzodiazepines).

